### Statistical Analysis

A descriptive analysis will be conducted to summarize the baseline characteristics of the 2 randomized groups. Continuous variables will be analyzed using means and standard deviations (assuming normality) or medians and interquartile ranges. Categorical variables will be analyzed using proportions and frequencies.

Primary analysis will be conducted according to the intention-to-treat principle. The 2 coprimary outcomes, change in VLUK from baseline and VeLUSET scores at 4 weeks, will be analyzed using generalized linear models with a Gaussian family and identity link, corresponding to an analysis of covariance framework. For each outcome, the post-intervention score at 4 weeks will be used as the dependent variable, with the treatment group as the main independent variable and the corresponding baseline score included as a covariate. In the event of an imbalance between the 2 groups, multivariate generalized linear models will be employed. The coprimary outcomes will be evaluated using a hierarchical testing strategy to control the family-wise type I error rate at 5%. Specifically, the between-group difference in VLUK will be tested first; only if this comparison reaches statistical significance will the coprimary outcomes be assessed at the same significance level (ie, 5%). The secondary outcomes assessed at follow-up will be analyzed, accounting for the repeated-measures structure of the data, with time treated as a categorical variable, using appropriate parametric methods for longitudinal data. When relevant, within- and between-group comparisons over time will be performed.

Comparisons of categorical outcomes, including healing status and recurrence, will be conducted using chi-square or Fisher exact tests, as appropriate. Secondary analyses will be considered exploratory, and no formal adjustment for multiplicity will be applied beyond the hierarchical testing of the coprimary end points.

The software R version 4.4.2 (2024-10-31 UCRT) has been selected to perform both design and data analysis.

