#### Randomization and Blinding

After obtaining informed consent and confirming eligibility criteria, randomization will be conducted using the REDCap (Research Electronic Data Capture; Vanderbilt University) platform. Patients will be randomly assigned to 1 of 2 parallel groups in a 1:1 ratio, using block randomization to ensure balance between the 2 groups during the follow-up.

The study is single-blind. Two separate teams, blind and unblind staff, will be created and assigned different activities to be performed. Nurses belonging to the blind staff will be responsible for assessing patients and delivering a blinded QR code, thereby preventing them from knowing which intervention is assigned to each participant. The unblind staff will have access to all other information except clinical assessments and will serve as the appointed contact point for patients and their caregivers regarding any study participation–related issues, thus preventing any potential risk of unblinding. Patients’ and caregivers’ questions (related to study participation or clinical care) will be directed only to the unblind staff. Both the blind staff and the patients or caregivers will be informed of this logistic before the study starts and reinforced during the study conduction and follow-up.

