### Sample Size Calculation

The primary end points are the mean differences in pre-post scores (collected after 4 wk of follow-up and at baseline) of the VLUK and the VeLUSET questionnaires, which are considered coprimary hierarchical end points. This implies that the mean difference in VLUK within the treatment group must be statistically greater than the mean difference in the control group before the mean difference in VeLUSET between the control and treatment groups is evaluated. An interim analysis has been planned at the halfway point of the enrollment. The interim analysis assumes the Lan-DeMets O’Brien-Fleming approximation alpha-spending function and includes an early efficacy stop in case *Z*>2.54. The nominal *P* values are .006 and .048 at the interim and final analyses, respectively. Moreover, the conditional power will be calculated, and resampling will be performed in case of 50%<conditional power<80%. Otherwise, the sample size will be kept at the original size (72 patients per group), as described in the following. Particularly, a type I error of 5%, a power of 80%, and a dropout rate of 10% have been considered for the sample size estimation.

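### Testing VeLUSET at a nominal 5% once VLUK succeeds ignores the interim look, so the promised 5% family-wise error is not guaranteed

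*Protocol article*

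**What the plan says.** Under Sample Size Calculation (protocol article), the pre-post changes in VLUK and VeLUSET at 4 weeks are the primary end points, "which are considered coprimary hierarchical end points": VLUK must succeed before VeLUSET is evaluated. The same paragraph states that "An interim analysis has been planned at the halfway point of the enrollment". It uses a Lan-DeMets O'Brien-Fleming "approximation alpha-spending function and includes an early efficacy stop" at Z>2.54, with nominal P values of .006 at the interim and .048 at the final analysis. It does not say which endpoint the Z belongs to.

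Under Statistical Analysis, the hierarchy is said to hold the family-wise error at 5%. VLUK is tested first, and "only if this comparison reaches statistical significance will the coprimary outcomes be assessed at the same significance level (ie, 5"%). That sentence mentions neither the two looks nor the levels .006 and .048. The article does not say what happens to VeLUSET if the trial stops at the interim.

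**The concern.** With a single analysis, a fixed sequence may pass the whole 5% to the second endpoint, because the time at which that endpoint is tested does not depend on the data. Here it does. If Z>2.54 is applied to VLUK, VeLUSET is tested on half the data when VLUK crosses early and on all the data otherwise.

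VLUK tends to cross early when the interim data happen to favour the video arm. If the two scores move together, VeLUSET is then also more likely to look favourable by chance. A nominal 5% for VeLUSET at the look chosen by VLUK can therefore exceed 5% overall. At stake is the confirmatory status of the self-care claim, which rests on the promised error control.

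**Working it through.** **Inputs from the article.** Type I error 5% (sidedness not stated), 72 patients per group, 10% dropout, interim at half of enrolment, Z>2.54, nominal levels .006 and .048, VeLUSET at 5% after VLUK.

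**Assumptions.** Information fraction t = 0.5 at the interim; Z>2.54 applies to VLUK; correlation ρ between the VLUK and VeLUSET statistics (the article gives none); no change of sample size at the interim.

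**Step 1: reproduce the stated boundaries.** The spending function is α(t) = 2[1 − Φ(z/√t)], where z is the upper α/2 point.
- One-sided 5%: z = 1.960, so 1.960/0.7071 = 2.772 and α(0.5) = .0056. The interim boundary is c1 = 2.538. The final boundary solves P(Z1 ≤ 2.538, Z2 ≤ c2) = 0.95 with correlation √0.5, giving c2 = 1.662 and nominal P = .0482. This matches 2.54, .006 and .048.
- Two-sided 5%: boundaries 2.963 and 1.969, nominal P = .0031 and .0490. This does not match.

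The stated figures are thus those of a one-sided 5% design.

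**Step 2: error for VeLUSET under the literal rule.** Let X1, X2 be the VLUK statistics at the two looks, with means θ√0.5 and θ. Let Y1, Y2 be the VeLUSET statistics with mean 0 (no effect). The chance of a false VeLUSET claim is

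P(X1 > c1, Y1 > d) + P(X1 ≤ c1, X2 > c2, Y2 > d),

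with d = 1.645 at both looks (one-sided 5%), or d = 1.960 with c1 = 2.963 and c2 = 1.969 (2.5% per side). Correlations: √0.5 between looks, ρ between endpoints at the same look, ρ√0.5 across both. The table gives the maximum over θ by numerical integration.

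| ρ (assumed) | One-sided 5%, VeLUSET at 5% | One-sided 5%, VeLUSET at 2.538 / 1.662 | 2.5% per side, VeLUSET at 2.5% |
|---|---|---|---|
| 0 | 5.0% | 3.0% | 2.5% |
| 0.3 | 5.3% | 3.1% | 2.7% |
| 0.5 | 5.6% | 3.3% | 2.9% |
| 0.7 | 6.0% | 3.6% | 3.1% |
| 0.8 | 6.3% | 3.9% | 3.3% |
| 0.99 | 7.6% | 4.8% | 3.9% |

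As ρ approaches 1, the one-sided literal rule reaches 7.9% and the look-specific rule 4.98%.

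**Step 3: power cost of the look-specific level at an early stop.** Evaluable patients per arm at the end: 72 × 0.9 = 64.8; at half enrolment about 32. For an assumed standardized VeLUSET difference d = 0.5, the drift is 0.5 × √(32/2) = 2.0.
- At nominal one-sided 5%: 1 − Φ(1.645 − 2.0) = 64%.
- At the interim boundary: 1 − Φ(2.54 − 2.0) = 29%.

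**The case against.** The strongest reply is that the same significance level may mean the same overall 5%, spent in the same way as for VLUK. On that reading the error is controlled, as the third column of the table shows. The article also never says in so many words that VeLUSET is tested at 5% at either look, and that Z>2.54 belongs to VLUK is an inference from the hierarchy. All this stands as a reason to call the excess a consequence of the literal reading. It does not remove the need to reconcile the sections: the sentence gives a number, 5%, that matches neither .006 nor .048.

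A second reply is that the excess is small. This is correct. Every figure is a maximum over the VLUK effect, there is no excess at zero correlation, and values near 7.6% need almost perfect correlation between a 15-item knowledge test and a 30-item self-efficacy tool. Still, both scores come from the same patients after the same education, so some positive correlation is plausible.

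Two stronger readings are tempting.
- A reader might infer that an early stop leaves VeLUSET underpowered. The article gives no effect size, standard deviation or named endpoint for its 80% power, so this cannot be shown. If VeLUSET is assumed to have the same 80%-power effect as VLUK, an interim stop occurs in about 22% of trials (one-sided). The chance of winning VeLUSET is then 59%, 63%, 67% and 73% at correlations 0, 0.3, 0.5 and 0.8, against 64%, 67%, 69% and 73% if VeLUSET always waited for the full sample. Most of the shortfall from 80% comes from the VLUK gate itself.
- A reader might infer a larger inflation from testing VeLUSET at 5% at both looks. The gate and the efficacy stop together exclude that.

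**Conclusion.** The point holds in a limited form. As written, the 5% level for VeLUSET does not fit the group-sequential plan, and the promised 5% family-wise error is not assured. With Z>2.54 applied to VLUK and half the information at the interim, the worst-case error is about 5.3% to 6.3% for assumed correlations of 0.3 to 0.8 on the one-sided 5% scale that reproduces the stated boundaries. With two-sided boundaries it is 2.7% to 3.3% instead of 2.5% per side. The disagreement between 5% and .048 at the final look does not depend on any assumed correlation. No claim about inadequate VeLUSET power follows from the document.

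**What to change.** Under Statistical Analysis, replace the closing 5% level with wording such as: *VeLUSET will be tested at the nominal level of the look at which it is evaluated, under the same Lan-DeMets O'Brien-Fleming spending function as VLUK (.006 at the interim, .048 at the final analysis).* Under Sample Size Calculation, state that Z>2.54 governs VLUK. Stating the sidedness there would also make clear which scale the levels are on.

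The text change is two sentences, and the article reports that no trial participants had been enrolled at submission. The statistical cost is the drop in interim VeLUSET power shown in step 3, from 64% to 29% under those assumptions.

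The sponsor should therefore also decide, and write down, whether an early VLUK win ends the trial or whether that result is kept and enrolment continues to 144 patients for VeLUSET. Either choice is legitimate. Under the equal-effect assumption above, the overall chance of winning VeLUSET with the look-specific levels is 51%, 55%, 59% and 66% (correlations 0, 0.3, 0.5, 0.8) if the trial stops on VLUK, and 64%, 67%, 69% and 73% if it continues. Continuing gives up the saving from an early stop, which is limited with a planned enrolment of about 6 months.

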#### Baseline Questionnaires

Patients who meet the eligibility criteria and consent to participate in the study will be requested by the researcher to provide sociodemographic and health-related data, including age, gender, level of education, occupation, with whom they live, presence of private or family care, preexisting pathologies, smoking habits, presence of pain, venous ulcer–related information, and medication management. The researcher will input these data and the Pressure Ulcer Scale for Healing (PUSH) Tool 3.0 measurement scale into the REDCap platform using a tablet provided by the company. To ascertain the level of knowledge about the disease, the level of self-care, and the patient’s well-being, the patient will be required to complete, respectively, the validated Venous Leg Ulcer Knowledge (VLUK) measurement scale, the validated Venous Leg Ulcer Self-Efficacy Tool (VeLUSET) measurement tool, and the WOW-I scale, using the company’s or their own smart device.

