#### Secondary Outcomes

Secondary outcomes (descriptive) include (1) VLUK and (2) VeLUSET scores at 3 and 6 months, (3) the evaluation of the healing process (PUSH Tool 3.0 score), and (4) improvements in well-being (WOW-I score) at 1, 3, and 6 months.

Moreover, the number of VLU recurrences in participants and the number of patients with complete healing will be assessed at 12 months of follow-up.

The instruments used to investigate the primary outcomes and well-being are self-administered questionnaires, while the healing process will be evaluated by the nurse using the PUSH Tool 3.0. The questionnaires and tools will be administered at the beginning of the study and at subsequent follow-up points, as described below in the study timeline.

Finally, the presence of any recurrence and complete healing will be investigated at the 12-month follow-up point through a single question asked by the nurse via telephone. No specific tools will be employed. The previously described evaluations will be conducted in both the intervention and control groups (Figure 1).

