##### PUSH Tool 3.0

The healing process will be documented within the study using the PUSH Tool 3.0, introduced in 1997 by the National Pressure Ulcer Advisory Panel and demonstrated to be an effective method for monitoring the healing of venous ulcers [26]. The tool was selected for its simplicity, speed, and reliability in monitoring venous ulcer healing. It comprises 3 items: lesion size (length × width), exudate quantity (none, light, moderate, and heavy), and tissue type (necrotic tissue, slough, granulation tissue, epithelial tissue, and closed). The total lesion score is obtained by summing the single-item scores, which range from 0 to 17. A reduction in the total score is indicative of progress toward the healing process.

If a patient achieves complete healing before the conclusion of the study, they will be classified as a “healed patient” and contacted again via telephone for follow-up purposes.

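### Twelve-month complete healing is compared without adjustment for the baseline PUSH score already collected, which forgoes some precision in an exploratory secondary outcome

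*Protocol article*

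**What the plan says.** Under Secondary Outcomes, the protocol article states that "the number of VLU recurrences in participants and the number of patients with complete healing will be assessed at 12 months of follow-up"; the information comes from a telephone question. The same section labels the secondary outcomes descriptive, and Statistical Analysis calls the secondary analyses exploratory. The method for healing is fixed there: "Comparisons of categorical outcomes, including healing status and recurrence, will be conducted using chi-square or Fisher exact tests, as appropriate".

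Under Baseline Questionnaires, "The researcher will input these data and the Pressure Ulcer Scale for Healing (PUSH) Tool 3.0 measurement scale into the REDCap platform", and Table 1 ticks PUSH at t0. The tool covers lesion size, exudate and tissue type: "The total lesion score is obtained by summing the single-item scores, which range from 0 to 17". A falling score marks progress toward healing.

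The coprimary scores are treated differently. They are modelled "with the treatment group as the main independent variable and the corresponding baseline score included as a covariate". The sentence that follows adds: "In the event of an imbalance between the 2 groups, multivariate generalized linear models will be employed".

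Allocation is 1:1, "using block randomization to ensure balance between the 2 groups during the follow-up". The article mentions no stratification by ulcer severity.

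**The concern.** A chi-square or Fisher test compares two raw proportions. If an ulcer's starting state predicts whether it has closed a year later, the crude test leaves that predictable variation in the noise. Any chance difference between the arms in starting severity also goes into the estimated healing difference. The plan already adjusts each coprimary score for its own baseline. Baseline PUSH is the natural counterpart for healing and is recorded anyway, but the stated method has no place for it. At stake are the width of the interval around the healing difference and how far that difference reflects the intervention rather than the luck of allocation.

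**Working it through.** **Inputs from the documents.** 72 patients per group and 10% dropout (Sample Size Calculation), so 72 × 0.90 = 64.8, taken as 65 evaluable per arm. The plan states no power or rate for healing, so there is no figure of its own to reproduce.

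**Assumptions.** Two-sided 5% test. Healing of 50% versus 70%, with 60% versus 80% as a second case. Baseline severity is a standard normal score entering the logit of healing with a coefficient of 0, 0.5, 1.0 or 1.5 per SD (none, weak, moderate, strong; AUC 0.50, 0.64, 0.74, 0.81).

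**Step 1: crude power by formula.** Power = Φ{[Δ − 1.96·√(2p̄(1−p̄)/n)] / √[(p₁(1−p₁) + p₂(1−p₂))/n]}. With p₁ = 0.5, p₂ = 0.7, p̄ = 0.6 and n = 65, the numerator is 0.2 − 1.96 × 0.0859 = 0.0316 and the denominator is 0.0841. Their ratio is 0.375, so power is 64.6%. For 60% versus 80% the same formula gives 70.6%.

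**Step 2: crude against adjusted, by simulation.** There were 4000 trials per setting. The uncorrected chi-square was compared with a likelihood-ratio test for arm in a logistic model containing the severity score. The variance ratio is that of the crude to the standardised risk difference. Results for 50% versus 70%:

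| Prognostic value | Crude power | Adjusted power | Variance ratio | 95% CI half-width, crude → adjusted |
|---|---|---|---|---|
| none | 64.0% | 63.8% | 0.99 | 16.5 → 16.6 points |
| weak | 64.7% | 67.2% | 1.04 | 16.4 → 16.1 points |
| moderate | 65.1% | 72.7% | 1.18 | 16.5 → 15.2 points |
| strong | 65.4% | 79.4% | 1.35 | 16.7 → 14.4 points |

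The half-width is 1.96 × the simulated SD of the estimate, for example 1.96 × 0.0840 = 16.5 points and 1.96 × 0.0773 = 15.2 points in the moderate row. For 60% versus 80%, crude power of about 71% becomes 73%, 78% and 84%. Over all settings with a prognostic score, the variance ratio runs from about 1.04 to 1.38.

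**Step 3: validity.** With 60% healed in both arms, the chi-square rejected in 4.9% to 5.3% of trials and the adjusted test in 5.2% to 6.0% (simulation error √(0.05 × 0.95/4000) = 0.3 points). The crude test holds its level. The adjusted likelihood-ratio test runs slightly high, so a small part of its power gain is a difference in size. The variance ratio and the half-widths do not depend on that.

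**Step 4: chance imbalance.** The SD of the between-arm difference in mean severity is √(2/65) = 0.175 SD, and a difference beyond 0.34 SD arises in about 5% of trials. With no treatment effect and 60% healing, a 0.34 SD imbalance alone shifts the healing difference by 3.9, 6.8 or 8.7 percentage points (weak, moderate, strong).

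**Step 5: a second set of assumptions.** About 50% healed in controls, conditional log odds ratio 0.9, Wald test, 2000 trials per setting. The chi-square and adjusted powers were 67.6% and 69.2%, 60.4% and 64.9%, 51.6% and 59.2%, and 45.8% and 57.0%, at baseline-outcome correlations of about 0.22, 0.33, 0.42 and 0.49. The gain is therefore about 2 to 11 points, the same order as in step 2.

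**The case against.** The strongest reply is that nothing here is wrong. An unadjusted comparison of two proportions is valid in a randomised trial, and chance imbalance is already part of its sampling error. The outcome is descriptive and exploratory, no power is claimed for it, and the sample size was set for the coprimary scores. The healing process also has a second analysis, PUSH over 1, 3 and 6 months, under the longitudinal methods. All of this stands. A reader might infer from the concern that the test is biased or that the trial's main conclusion is at risk; step 3 and the coprimary status of VLUK and VeLUSET rule out both. A reader might also take healing to be the main clinical outcome, but the article lists it among other secondary outcomes and ranks none above the rest.

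The size is also fairly questioned. Nothing in the documents shows that baseline PUSH predicts a telephone answer a year later. The simulations favour adjustment, because the fitted model matches the one that generated the data, whereas PUSH is a bounded sum. At the weak end the gain is slight.

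Two replies carry less weight. The first is that the imbalance sentence may cover healing. It names no outcome, so this cannot be excluded outright. But it stands within the coprimary text, before the longitudinal analysis of secondary outcomes is introduced, and it names no covariate. Even read generously, it makes adjustment depend on an observed imbalance and sits awkwardly with the named chi-square or Fisher test. The second is that such detail belongs in an analysis plan that is not shown. The article does not leave the method open; it names one.

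**Conclusion.** The point holds as a cheap improvement, not as an error. The plan fixes an unadjusted test for 12-month healing while collecting a baseline measure that could sharpen the comparison. Under the assumptions above, the gain for 50% versus 70% healed is about 2 to 14 power points, or 0.3 to 2.3 percentage points off the confidence interval half-width. It falls to nothing if PUSH does not predict healing. The healing rates and the prognostic strength are assumed, because the documents give neither. The test's validity and the coprimary conclusions are not in question.

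**What to change.** In Statistical Analysis, prespecify for 12-month complete healing a logistic regression on treatment arm and baseline PUSH total score. Report the odds ratio and the standardised (marginal) risk difference, each with a 95% CI. Keep the crude proportions and the chi-square or Fisher result as supportive. State that the adjustment is made whether or not the arms differ at baseline, so that the covariate is not chosen after the data are seen.

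The cost is one sentence of wording and slightly more analysis work, with no new data, visits or patients. It is not entirely free: the adjusted odds ratio is conditional on PUSH and is not the same quantity as the crude one, which is why the standardised risk difference should be reported beside it. At manuscript submission no participant had been enrolled in the main trial, so the change could be made before any outcome data exist.
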